### Ethics approval

The study protocol was prospectively approved by the ethical committee at Charles Nicolle university hospital of Tunis, Tunisia (approval number FWA 00032748 -IORG0011243) (attached S5 and S6 Files).

A Data Monitoring Committee (DMC) will not be established for this trial because the risk to participants is minimal. Monitoring of adverse events and safety data will be conducted by the research team, in accordance with standard protocols. Any concerns regarding patient safety will be directly reported to the ethics committee.

## Discussion

This trial aims to investigate the role of low pressure pneumoperitoneum in reducing postoperative pain after laparoscopic cholecystectomy. We hypothesize that low pressure pneumoperitoneum at 8 mmHg reduces postoperative pain, without increasing operation time or postoperative morbidity.

If low pressure pneumoperitoneum is shown to effectively improve postoperative pain after LC, it could lead to several positive outcomes. This includes a potential reduction in the consumption of postoperative pain killer and the duration of hospital stay. In fact, one of the most reported causes of failure of ambulatory cholecystectomy is postoperative pain [11]. These improvements could translate into significant cost-savings for healthcare systems.

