## Abstract

**Background:**

Laparoscopic cholecystectomy is the gold standard for treating symptomatic gallstone disease. Pneumoperitoneum is essential for adequate visualization during the procedure and is typically maintained at a standard pressure of 12–14 mmHg. However, high insufflation pressure may contribute to increased postoperative pain. This study aims to assess whether low-pressure pneumoperitoneum (8 mmHg) reduces postoperative pain compared to standard pressure (14 mmHg), without compromising operative safety or efficacy. We hypothesize that low pressure pneumoperitoneum at 8 mmHg reduces postoperative pain, without increasing operation time or postoperative morbidity.

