**Conclusion:**

If proven effective, low-pressure pneumoperitoneum may represent a simple strategy to improve postoperative comfort in laparoscopic cholecystectomy without compromising surgical outcomes.

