## Introduction

Laparoscopic cholecystectomy is the gold standard for symptomatic gallstones [1]. It involves the use of Carbone dioxide to inflate the peritoneal cavity to create a pneumoperitoneum in order to provide an adequate visualization and a sufficient space for working. There is no consensus on the optimal pressure of the pneumoperitoneum, but the standard varies between 12 and 14 mmHg [2]. Different studies have demonstrated that high pneumoperitoneum pressure is associated with postoperative morbidity, particularly cardiopulmonary complications and postoperative pain [3]. For this reason, the low impact surgery concept has emerged [4]. Several meta-analyses have compared low pressure versus standard pressure in laparoscopic cholecystectomy and the results were controversial, with high risk of bias across studies [2,5].

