#### Secondary endpoints.

postoperative pain at H12: defined as abdominal and/or interscapular pain measured by a Visual Analog Scale (VAS) as following: 0 no pain, 10 worst possible painPostoperative pain at H24: defined as abdominal and/or interscapular pain measured by a Visual Analog Scale (VAS) as following: 0 no pain, 10 worst possible painvomiting: Assessed by: Postoperative Nausea and vomiting (PONV) score defined as follow: 0 no PONV, 1 moderate nausea, 2 moderate vomiting, 3 uncontrollable nausea and/or vomitingConversion rate to open procedureOperative timemorbidity: defined by any surgical complications assessed within 30 days postoperativelypostoperative length of stay

All data will be recorded on a dedicated data collection form (attached S4 File). Patient data will then be analyzed in an anonymized SPSS file.

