### Statistical methods

#### Sample size and power.

Using the VAS scale, the mean value of abdominal pain after laparoscopic cholecystectomy with a pressure of 14 mm Hg is estimated in the literature at **4.1 + /-1.8** (H6) [9]. We hypothesize that patients in the low-pressure group will experience significantly lower postoperative pain compared to those in the standard-pressure group (14 mm Hg), with no increase in postoperative morbidity. The difference of means (Δ) is estimated to “01”. For a power level of 90%, a significance level of 5% and a two-way comparison between the two arms of the study, 70 patients/group are needed, i.e., 140 in all. Sample size was overestimated by 20% as per loss of follow-up and/or data discrepancies expectation. An overall sample size of 170 subjects will be enrolled in the study, divided into 85 experimental group vs. 85 placebo group [10]. Allocated study subjects were randomly assigned by, using simple 1:1 non-stratified sequence and a block size of 4.

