### Secondary endpoints

**Change of VAS over time:** To evaluate the temporal evolution of VAS (at H6, H12 and H24), analysis of variance (ANOVA) with Bonferroni adjustment will be performed. This statistical approach is particularly suited to repeated measures data.Nausea and vomiting: Changes from baseline (H0) to the final time point (H4) will be analyzed within groups using paired ANOVA tests. Between-group comparisons of these changes will be performed using independent ANOVA tests.Duration of hospital stay: the mean hospital stays in each group (control vs intervention) will be compared using t-tests or non-parametric test U of Mann and Whitney when appropriate.Operative time: the mean operative time in each group (control vs intervention) will be compared using t-tests or non-parametric test U of Mann and Whitney when appropriate.Conversion rate: the frequency of conversion rate in each group will be compared by chi²test or fisher exact test when appropriate.30-day morbidity: the frequencies of each postoperative complication in each group will be compared by chi²test or fisher exact test when appropriate.

The statistical analysis will be conducted using SPSS version 26. Analyses will be performed by an independent investigator (CD in the authors’ list) blinded to treatment allocation, ensuring unbiased interpretation of the data.

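### The no-increase claim for morbidity and operation time is paired only with two-sided difference tests, so a non-significant result cannot support it; for morbidity the trial is also too small to be reassuring

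*Protocol article*

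**What the plan says.** The no-increase claim appears in several places in the protocol article:

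- Discussion: "We hypothesize that low pressure pneumoperitoneum at 8 mmHg reduces postoperative pain, without increasing operation time or postoperative morbidity". The abstract's Background carries the same hypothesis and frames the aim as less pain "without compromising operative safety or efficacy".
- Sample size and power: lower pain is expected "with no increase in postoperative morbidity". No morbidity rate, margin or power accompanies this.
- Abstract, Conclusion: if effective, low pressure may "improve postoperative comfort in laparoscopic cholecystectomy without compromising surgical outcomes".

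The section headed Hypothesis and the Aim mention pain only. The article is therefore not consistent on whether no increase is a hypothesis of the trial.

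For the analysis, the endpoint list defines morbidity as "any surgical complications assessed within 30 days" of surgery. The statistical section then says that "the frequencies of each postoperative complication in each group will be compared by chi²test or fisher exact test when appropriate". Operation time gets a t-test or Mann–Whitney test, and conversion a chi-square or Fisher test. The Data analysis framework makes every test two-sided at 0.05 and adds, in general terms, that complications will be compared by chi-square or Fisher.

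**The concern.** A two-sided difference test can show that the arms differ. Failing to show it is not evidence that they are alike, least of all in a small sample with rare events. To support a no-increase claim, the plan needs either a margin that the confidence interval must exclude or an interval narrow enough to be informative. The article sets neither, and its sample size was chosen for another endpoint.

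Testing each complication separately makes this worse. The per-patient composite in the endpoint list has more events than any of its components, yet the statistical section specifies tests on the components.

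At stake is the safety half of the message. The trial could report less pain together with a non-significant morbidity comparison, and its own framing would invite the conclusion that safety is unchanged, although the data might be compatible with a sizeable increase.

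**Working it through.** **1. What the sample size covers.** Inputs from Sample size and power: difference 1 VAS point, SD 1.8, two-sided 5%, power 90%. Normal formula: n = 2 × (1.960 + 1.282)² × 1.8² / 1² = 68.1, so 69 per arm. The t-based solution is 69.06, so 70. The stated 70 per arm is reproduced (power 90.8%). Enrolment is 85 per arm. Morbidity, conversion and operation time do not enter this calculation.

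**2. Power for morbidity.** The protocol gives no rate, so the rates here are assumptions: a doubling from a base of 2%, 3%, 5% or 10%. Both planned tests are shown, at 70 and at 85 per arm. Fisher power is by exact enumeration. Chi-square power is Φ{[d√n − 1.96√(2p̄(1 − p̄))] / √(p₁(1 − p₁) + p₂(1 − p₂))}, where d = p₂ − p₁ and p̄ is the mean of the two rates.

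| Assumed rates | Fisher, 70 | Fisher, 85 | Chi-square, 70 | Chi-square, 85 |
|---|---|---|---|---|
| 2% vs 4% | 1.8% | 3.0% | 10.2% | 11.6% |
| 3% vs 6% | 4.7% | 6.9% | 13.4% | 15.4% |
| 5% vs 10% | 11.4% | 15.7% | 20.0% | 23.4% |
| 10% vs 20% | 30.5% | 37.2% | 38.0% | 44.6% |

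The range is about 2% to 45%. In every cell a doubling is more likely to be missed than detected. Detecting 5% vs 10% with 80% power would need 435 per arm. The top row also shows what happens when the composite is split into single rare complications.

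**3. Precision for morbidity.** The half-width of the 95% interval for the risk difference, with equal rates p, is 1.96 × √(2p(1 − p)/n). At p = 5% and n = 85 this is 1.96 × √(2 × 0.05 × 0.95/85) = 0.0655, or about ±6.6 points; at n = 70 it is ±7.2. With identical observed rates of 5%, the upper limit would still exceed the 5-point rise that a doubling represents. At 2% the half-width is 4.2 to 4.6 points, and at 10% it is 9.0 to 9.9.

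**4. What a formal no-increase claim for morbidity would need.** Per arm, with one-sided 2.5%, 80% power and equal true rates of 5% (assumed): (1.960 + 0.842)² × 2 × 0.05 × 0.95 / margin². This gives 829 for a 3-point margin, 299 for 5 points and 75 for 10 points. Only the widest of these is within reach.

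**5. Operation time.** Power for a 0.5 SD difference is Φ(0.5 × √(n/2) − 1.96), which is 84% at 70 per arm and 90% at 85. The protocol gives no SD. Assuming 15 to 30 minutes, the interval half-width 1.96 × SD × √(2/n) at 85 per arm is 4.5 to 9.0 minutes. A margin-based conclusion may be feasible here, depending on the SD and the margin chosen.

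**The case against.** The strongest reply is that the formal Hypothesis and Aim concern pain only, that these outcomes are secondary, and that an article may leave margins and interval reporting to a fuller plan. That is fair up to a point: the absence of risk differences and intervals would not by itself be a finding. But this article itself makes the no-increase claim in the abstract, the sample-size section and the Discussion, and itself fixes the tests. The two do not match.

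Several stronger readings are tempting, and the documents do not support them:

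- **A single power figure.** A reader might quote about 16% power as a property of the trial. It holds only for an assumed 5% vs 10%, Fisher's test and 85 per arm, and it does not apply to operation time.
- **A near-certain miss.** A reader might infer that a doubling of morbidity would almost certainly go unseen. From 10% to 20% at 85 per arm, the chance of missing it is 55% (chi-square) to 63% (Fisher).
- **A stated decision rule.** Nowhere does the article say that non-significance will count as proof of safety. The abstract's conclusion is conditional, and the risk is inferred from the framing.
- **An endpoint never compared.** The framework's general reference to complications, and the recording of whether complications occurred within 30 days, could cover the per-patient composite. The text is unclear rather than silent.
- **Missing cardiopulmonary events.** The Introduction links high pressure to morbidity, "particularly cardiopulmonary complications and postoperative pain", while the endpoint speaks of surgical complications. Omitting these events would mainly hide a benefit of low pressure, so it does not add to false reassurance. The exclusion also rests on one adjective: the abstract and data-collection section do not restrict 30-day events in this way.

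**Conclusion.** The point stands in this form: the no-increase claim cannot be supported by the analyses as written. For morbidity the mismatch is serious, because power to detect a doubling is only about 2% to 45% and the interval at 5% morbidity is about ±6.6 points at 85 per arm. Those figures rest on assumed rates, but the conclusion is the same across the range. For operation time the fault is the missing margin or interval criterion, not generally low power. The primary pain comparison is unaffected. This should be corrected, because it bears on the safety statement that would accompany any positive pain result.

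**What to change.** The Trial status section says that analysis follows the end of follow-up, so the changes belong before unblinding:

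1. Compare the endpoint as defined, patients with at least one 30-day complication, as a risk difference with 95% interval. List individual complications descriptively. Make the statistical section and the Data analysis framework agree on this.
2. Reword the abstract (Background and Conclusion), the sample-size section and the Discussion so that morbidity and conversion are estimated, not shown to be unchanged. This also brings them into line with the pain-only Hypothesis.
3. For operation time, either prespecify a justified margin and conclude no increase only if the upper 95% limit lies below it, or report the difference with its interval and drop the claim.

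The cost is wording, possibly one agreed margin, and a more modest safety conclusion. No extra patients are needed.

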### Trial status

As of the time of this publication, the study is actively underway in accordance with protocol version. Recruitment of participants started in November 1st, 2024 and is anticipated to be completed by December 2025. The intervention phase and the last follow-up assessments are expected to be concluded by January 2026. The study is progressing according to the planned timeline, and data collection and analysis will commence thereafter to generate meaningful results which will be published.
